# Effect of alkalized urine on renal calculi in patients with gout: a protocol for a placebo-controlled, double-blinded randomized controlled trial

**DOI:** 10.1186/s13063-021-05721-8

**Published:** 2021-10-26

**Keywords:** Gout, Renal calculus, Urine alkalization, Sodium bicarbonate

## Abstract

**Background:**

The prevalence of renal calculi in patients with gout is high. Alkalized urine has been recommended by the 2020 European Association of Urology (EAU) guidelines to promote calculus dissolution. However, randomized controlled trials are lacking.

**Methods:**

In the protocol of this randomized, placebo-controlled, double-blinded trial, patients with gout combined with renal calculi are randomized (1:1) to the placebo and sodium bicarbonate groups. The intervention would be performed for 24 weeks, the 1–12 weeks are double-blinded, and the 13–24 weeks are open-labeled. Sodium bicarbonate (1 g tid) will be performed for 24 weeks in the sodium bicarbonate group. The placebo will be performed for 12 weeks and not be performed from 13 weeks to 24 weeks in the placebo group. All subjects will be administered febuxostat (40 mg/day) for 24 weeks and receive concomitant anti-inflammatory prophylaxis therapy for 12 weeks. The primary outcome is the proportion of patients whose renal calculus volume will be reduced after 12 weeks of treatment. The secondary outcomes include the volume changes of renal calculi, uric acid changes, the proportion of patients with serum uric acid (sUA) levels < 360 μmol/L, the changes in estimated glomerular filtration rate (eGFR), the pH value of urine, and the incidence of adverse events after treatment for 12 and 24 weeks.

**Discussion:**

This study will evaluate the efficacy and safety of sodium bicarbonate-alkalized urine on renal calculi in patients with gout.

**Trial registration:**

ClinicalTrials.gov ChiCTR2100045183. Registered on April 7, 2021, with ChiCTR.

## Introduction

### Background and rationale {6a}

Gout is caused by disorders of purine metabolism, increased uric acid production, and/or decreased uric acid excretion, leading to elevated sUA levels, forming monosodium urate (MSU) crystals that are deposited in the joints and kidney and other tissues. A meta-analysis reported that the pooled prevalence of gout was 1.1% in China [1].

Nephrolithiasis is common in patients with gout. It has been showed that 24% of patients with gout are suffering from nephrolithiasis. The odds ratio (OR) of gout as a risk factor for nephrolithiasis was 2.4 1 [2], and the hazard ratio (HR) of renal calculus as a risk factor for the development of end-stage renal disease (ESRD) was 2.34–6.18 [3]. More than half of the patients with nephrolithiasis carried bilateral and multiple calculi [4]. The formation of renal calculi in patients with gout is mainly related to high level of uric acid. A previous study analyzed uric acid composition in gout patients by DECT and found that the proportion of pure and mixed uric acid in renal calculus was 77.8% [5]. The ionized forms of uric acid readily form salts, namely monosodium urate, disodium urate, or potassium urate. Sodium is the dominant cation in the extracellular fluid. It is estimated that 98% of uric acid forms monosodium urate at pH=7.4, and the saturation of monosodium urate in the human plasma is about 7 mg/dL. As urine is acidified along the renal tubules, a portion of urate is converted to uric acid. The solubility of uric acid in aqueous solution is less than that of urate, but the saturation increases significantly with the increase in the pH value of urine. At pH 5, the urinary saturation of uric acid is 15 mg/dL, while the value reaches 158–200 mg/dL at pH7, with an increase of uric acid solubility by 20-fold [5]. Gout patients with long-term high uric acid levels also have elevated urinary uric acid concentration and form crystals after exceeding the solubility, gradually enlarged to shape calculus [6]. Previous studies have shown that the course of gout and low pH value of urine [5] are the primary hazard factors of renal calculus.

Another study suggested that the pH value of urine increased from 5.5 to 6.0 by administering sodium bicarbonate (1 g tid) for 3 months in gout patients [7]. Although several urological associations recommended urine alkalization to promote calculi dissolution in nephrolithiasis [8–11], advanced evidence is lacking. Since alkaline urine may increase the risk of hypertension, water-sodium retention, and heart failure, according to the 2020 American College of Rheumatology (ACR) guideline, starting alkalizing urine is not recommended even in cases of stimulated uric acid excretion. Based on the composition, renal calculus is mainly divided into calcified calculi, urate calculi, cystine calculi, and combinations. Typically, nephrolithiasis is assessed by ultrasonography, plain film radiography, tomography, or excretory urography with an intravenous contrast agent [12]. However, none of these methods could identify calculi before treatment. Dual-energy computed tomography (DECT) is a novel non-invasive technique that fundamentally distinguishes the composition of urate calculi. This method has been previously validated in both in vitro and in vivo studies [12–15]. Moreover, it can also be used to calculate the volume of renal calculi. The present study aimed to determine the effect of sodium bicarbonate-alkalized urine on renal calculus in patients with gout.

### Objectives {7}

The present study aims to determine the effect of sodium bicarbonate-alkalized urine on renal calculus in patients with gout.

### Trial design {8}

This 12-week dual-center, double-blinded, placebo-controlled and two-arm randomized trial (RCT) will be completed at the Shenzhen Traditional Chinese Medicine Hospital and People’s Hospital of Longhua District Shenzhen. A total of 98 patients with gout combined with renal calculi who meet the study criteria will be randomized (1:1) to the placebo and sodium bicarbonate group. The intervention would be performed for 12 weeks with a follow-up of 24 weeks. The 1–12-week group is double-blinded, and the 13–24-week group is open-labeled (Fig. 1).

**Fig. 1 Fig1:**
[figure not shown]
Trial flow and study design

## Methods: participants, interventions, and outcomes

### Study setting {9}

This study will be completed at the Shenzhen Traditional Chinese Medicine Hospital and People’s Hospital of Longhua District Shenzhen from April 30, 2021, to April 30, 2024.

### Eligibility criteria {10}

#### Inclusion criteria

Participants who meet the following criteria will be included:

(1) Male and female patients aged 18–80 years old.

(2) The diagnosis meets the 2015 European League Against Rheumatism (ELAR)/ACR criteria for acute arthritis of gout.

(3) B-ultrasound suggesting renal calculi.

(4) Male with no fertility requirement in recent 6 months.

(5) Female who have undergone sterilization operation or have been menopausal for 2 years.

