#### Research procedures

(1) Screening: In line with 2015 ACR and EULAR criteria and the score system for acute arthritis of gout, B ultrasonography suggests renal calculi. The patients are 18–80 years old.

(2) Enrolment: Each subject will be interviewed by investigators prior to the start of the treatment, and the data would be input into the database along with baseline data. The subjects will be divided into test and control groups according to the treatment, and both groups will be treated for 6 months. Renal calculus volume changes before and after treatment will be observed and recorded, respectively.

(3) Treatment scheme: Test group: sodium bicarbonate 1 g tid combined with febuxostat 40 mg/day and prednisone acetate 5 mg Qd for 12 weeks. Control group: placebo 1 g tid combined with febuxostat 40 mg/day and prednisone acetate 5 mg Qd for 12 weeks.

(4) Laboratory indicators: Vital signs (pulse, blood pressure, temperature, respiration, and gout flares), four physiological indicators of blood lipids (TC, TG, HDL-C, LDL-C), fasting blood glucose, blood routine (RBC, WBC, NEUT, PLT, Hb), urine routine (pH value of urine, PRO, BLD), renal function (BUN, CREA, sUA, EGFR), liver function (ALT, AST, GGT, ALP), erythrocyte sedimentation rate (ESR), C-reactive protein (CRP), and renal DECT (location, size, quantity component of renal calculi).

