##### Secondary outcomes

The volume changes of renal calculi, uric acid changes, and the proportion of patients whose sUA levels are <360 μmol/L, the changes in eGFR, the pH value of urine, and adverse effects after 12 and 24 weeks of treatment. Adverse events will be monitored during the 24 weeks of treatment, including the incidence of hypertension before and after treatment, the incidence of post-treatment edema, and the rate of acute gout attack within 12 weeks. Any adverse reactions that occur during the study will be recorded in the “Adverse Reaction Table,” and the patients will be followed up until symptoms disappear or indicators return to normal. In the event of serious adverse events, necessary measures will be taken immediately to ensure the safety of the subjects. In addition to evaluating the primary and secondary outcomes, safety assessment will be conducted at baseline and at 24 weeks after treatment with respect to blood pressure, respiration, heart rate, blood routine, urine routine, liver and renal function, ESR, CRP, and renal DECT.

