#### Recruitment {15}

The randomized controlled trial that is blinded to assessors and patients will be conducted at the Shenzhen Traditional Chinese Medicine Hospital and People’s Hospital of Longhua District Shenzhen, wherein medical service would be provided for patients with gout combined with renal calculi. The subjects in this study will be recruited from outpatient and inpatient by placing advertisements on social media platforms of the hospital departments and distributing posters in public areas of the hospital with details of the study and contact information.

Subjects interested will be welcome to contact the investigators by phone or on-site for initial screening. Potential participants would be enrolled, and an appointment was made with a designated physician to examine the inclusion and exclusion criterion. Patients who meet the criteria will be invited to participate in the study, and details of the RCT protocol will be provided. All subjects will be required to sign an informed consent and provide complete information. The subjects will be randomized (1:1) to the placebo and sodium bicarbonate group, and none of the patients would know about their assigned group. Then, the baseline characteristics will be assessed and a database record is obtained by the same physician. All subjects will be treated for 24 weeks and followed up on 4, 12, and 24 weeks, and the data will be evaluated. In addition, all subjects will be given a schedule of intervention dates and follow-up appointments. These evaluations will be performed by an assistant who is involved neither in the randomization nor in the treatment.

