## Discussion

In patients with gout, vascular injury caused by hyperuricemia and the deposition of urate crystals in the medulla is a major cause of substantial kidney damage, increasing the risk of chronic kidney disease and thus exerting a significant impact on the living quality of patients. Xanthine oxidase inhibitors alone are not as effective as alkalizing urine drugs in preventing renal calculi. Commonly used drugs include sodium bicarbonate and potassium sodium hydrogen citrate. However, both drugs give rise to adverse reactions, resulting in poor patient compliance [16]. Furthermore, recommendations by the 2020 ACR and EAU guidelines for the therapy of renal calculi in gout patients by alkalizing urine are controversial [10, 11]. Due to the lack of strong evidence, we have designed a RCT to analyze the effect of urine alkalization on renal calculi in gout patients by evaluating whether the renal calculus volume is reduced after 12 weeks of treatment. This study will provide guidance on the use of accurate medical methods such as urine alkalization for patients, thereby reducing the incidence of gout flares.

Nevertheless, the present study has some limitations. First, the universality of the sample population and the research centers involved in the trial is limited. In order to complete this clinical trial successfully, the selected participants should be local residents from Shenzhen, which will ensure their participation throughout the treatment. Patients with gout combined with renal calculi under investigation may not have urate calculi, as identified by DECT. In addition, the EAU guideline recommends administration of allopurinol during ULT, requiring the sUA level of each case meeting the standard (> 4.0 mmol/day and/or > 380 μmol/L) [11]. Previous studies have shown that gout patients have a high rate of sUA less than 360 μmol/L who have been treated with febuxostat (40 mg/d) in China [17]. Taken together, this clinical trial aims to explore if urine alkalization is suitable for patients with gout combined with renal calculi and whether the associated adverse events can be avoided. Finally, we hope that clinicians and gout patients can focus on the treatment of alkalized urine for renal calculi.

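### No entry criterion requires a stone that DECT can measure, although the primary outcome is a change in stone volume; stone composition also has no pre-specified role

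*Protocol article*

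**What the plan says.** The stone criterion under Inclusion criteria is "B-ultrasound suggesting renal calculi", and the screening step under Research procedures repeats it: "B ultrasonography suggests renal calculi". The exclusion criteria set an upper size limit of 15 mm but no lower limit, and none mentions DECT.

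DECT appears as a study measurement under Research procedures, "renal DECT (location, size, quantity component of renal calculi", and in the list attached to "safety assessment will be conducted at baseline and at 24 weeks after treatment" under Secondary outcomes. Background and rationale {6a} says that ultrasound and the other conventional methods could not identify the stones before treatment, and that DECT distinguishes urate stones and can calculate stone volume.

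The primary outcome is the proportion of patients whose stone volume is reduced after 12 weeks. Section {20c} defines the intention-to-treat set as all randomised patients and handles missing values by multiple imputation.

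On composition, Background and rationale {6a} cites an earlier DECT study in gout in which "the proportion of pure and mixed uric acid in renal calculus was 77.8" per cent. The Discussion concedes: "Patients with gout combined with renal calculi under investigation may not have urate calculi, as identified by DECT".

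**The concern.** The trial selects patients with one imaging method and measures its endpoint with another. Ultrasound may suggest a stone that DECT does not show, or does not show well enough to give a volume. Such a patient meets every criterion, is randomised and belongs to the intention-to-treat set, yet has no baseline from which a reduction could be judged.

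The article does not say how that patient counts. Each option has a cost:

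- Counting the patient as not reduced pulls both arms towards zero and shrinks the difference.
- Multiple imputation assigns a result to a stone that nobody measured. If the imputation model leaves out treatment arm, it also pulls the arms together.
- Dropping the patient departs from the all-randomised set and loses sample size.

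A second, lesser matter concerns interpretation. The mechanism under test is the rise in uric-acid solubility with urine pH. If the overall result is null and composition has no planned role, the reader cannot tell an ineffective treatment from a sample with many stones that alkalisation was not expected to dissolve.

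**Working it through.** **Inputs.** From Sample size {14}: response rates 89.74% and 64.10%, two-sided 0.05, power 80%, allocation 1:1, dropout up to 15%, 49 per group. From Background and rationale {6a}: 77.8%. The shares of 5%, 10% and 20% without a measurable stone are assumed.

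**1. The plan's own figure.** The pooled two-proportion formula is n = [1.96·√(2p̄(1−p̄)) + 0.8416·√(p₁(1−p₁)+p₂(1−p₂))]² / (p₁−p₂)². With p₁ = 0.8974, p₂ = 0.6410 and p̄ = 0.7692, this gives 41.2, so 42 per arm. The article's 84 for the control group fits 1:1 allocation only as the total, 2 × 42. Then 42 × 1.15 = 48.3, so 49. Exact power of the uncorrected Pearson test at 42 per arm is 83% (normal approximation 81%).

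**2. No measurable stone, counted as not reduced.** Both rates are multiplied by (1 − m). Power is exact, at 42 per arm.

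| Assumed m | Rates | Difference | Power |
|---|---|---|---|
| 0 | 89.7% vs 64.1% | 25.6 points | 83% |
| 5% | 85.3% vs 60.9% | 24.4 points | 73% |
| 10% | 80.8% vs 57.7% | 23.1 points | 64% |
| 20% | 71.8% vs 51.3% | 20.5 points | 51% |

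With all 49 per arm contributing, the four powers are 88%, 79%, 71% and 55%.

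**3. The same patients dropped.** The rates stay at 89.74% and 64.10% and only the sample size falls: 42 × 0.95 = 39.9, 42 × 0.90 = 37.8 and 42 × 0.80 = 33.6. Exact power at 40, 38 and 34 per arm is 81%, 78% and 75%.

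**4. Composition, two readings of the preliminary rates.**

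- Suppose those rates came from uric-acid stones only, and 22.2% of trial patients (100 − 77.8) have other stones that respond at the control rate in both arms. The treated rate becomes 0.778 × 0.8974 + 0.222 × 0.6410 = 0.8405. The difference is 84.05 − 64.10 = 19.95 points, and exact power at 42 per arm is 56% (63% at 49).
- Suppose instead that the preliminary sample had the same mix. The dilution is then already in the stated rates and power stays at 83%. The effect in uric-acid stones would be 25.64 / 0.778 ≈ 33 points, which no stated analysis estimates.

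**The case against.** **The all-stones population is the stated one.** The title and the Objectives concern renal calculi in gout, not uric-acid calculi, and the Discussion discloses that some stones may not be urate. This stands. Enrolling all stone types is a legitimate choice, so composition is secondary here and no restriction to uric-acid stones is proposed. It does not answer the measurability point, which applies to any stone type.

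**The power losses are conditional.** This also stands. The preliminary sample is not described. The 77.8% is worded as a proportion in calculi, and the same section says that more than half of patients with nephrolithiasis have bilateral and multiple stones, so it need not be a share of patients. No source gives the share without a DECT-measurable stone, and counting such patients as not reduced is not a rule in the article. A reader might infer that power is in fact 56% or 51%; the documents do not support that.

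**Timing of the scan.** A reader might infer that the baseline DECT comes after randomisation. Recruitment {15} says "The subjects will be randomized (1:1) to the placebo and sodium bicarbonate group" and next "Then, the baseline characteristics will be assessed and a database record is obtained by the same physician". That sentence does not name DECT, and the schedule figure is not available in the text reviewed, so the order is only suggested. The point does not need it: a scan taken before randomisation but not used for entry leaves the same gap.

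**Composition could still enter an analysis.** Section {20b} plans a multivariable logistic regression with variables chosen after univariate screening, and a statistical analysis plan may add subgroup reporting. Composition could come in that way, so it would be too strong to say that it can play no part. Data-driven entry is not a pre-specified role, however. Eligibility is a protocol decision, and an analysis plan cannot supply a baseline volume that was never measurable.

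**Conclusion.** The point holds on measurability. As written, the plan allows randomisation of patients for whom the primary outcome is undefined, and keeps them in the primary analysis set.

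The size is unknown because the share of such patients is unknown. Over an assumed 5% to 20%, the loss runs from about 2 percentage points of power (5%, dropped) to about 32 (20%, counted as not reduced), from a base of 83% at 42 per arm.

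The lack of a pre-specified role for composition is a secondary weakness. Its effect on power ranges from none to a fall to 56%, depending on which stones the preliminary rates came from, on reading 77.8% as a share of patients, and on non-uric-acid stones having the control rate and no treatment effect. The documents settle none of these.

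This should be corrected. It is a gap in design with a conditional cost, not a demonstrated loss of power.

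**What to change.** Make the planned baseline DECT a screening step before randomisation, and add an inclusion criterion of at least one stone with measurable DECT volume. Keep the all-stones population as primary.

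Pre-specify DECT composition (uric-acid-containing or not) as a factor in the primary analysis, for example by a Mantel–Haenszel test or a logistic model in place of the unstratified Pearson test. Report the effect in uric-acid-containing stones, with its confidence interval, beside the overall effect.

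For patients already randomised, define the primary analysis set from the pre-treatment DECT, with measurability decided blind to arm, and state this departure from the all-randomised set.

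The cost is some scans in patients who then fail screening, and changes of wording in the eligibility and analysis sections. The scan and the composition reading are already planned.

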#### Exclusion criteria

Potential subjects will be excluded if they meet any of the following:

(1) Allopurinol, probenecid, benzbromarone, and febuxostat tablets have been used for urate-lowering treatment (ULT) in the first 4 weeks of enrolment.

(2) Renal calculus >15 mm, obstruction (hydronephrosis), pain, and urinary tract infections requiring lithotripsy [10].

(3) Patients with secondary hyperuricemia caused by kidney disease, hematopathy, some medications, tumor chemoradiotherapy, and organ transplantation.

(4) Patients with a history of cardiocerebrovascular diseases, such as stroke, TIA, MI, and HF (NYHA II-IV), coronary artery surgery (for example, angioplasty, stent implantation, and bypass grafting).

(5) Patients with histories of peptic ulcer and gastrointestinal bleeding.

(6) Patients with active stage of liver disease and abnormal liver function or with a transaminase level of 1.2-fold higher than the upper limit of normal value.

(7) Patients with abnormal renal function and eGFR <30 mL/min.1.73 m^2^.

(8) Patients with malignant tumor or psychosis.

(9) Patients being allergic or intolerant to febuxostat.

(10) Patients with other (non-gout) chronic arthritis, acute inflammatory arthritis, and autoimmune diseases associated with arthritis.

(11) Patients who take or need azathioprine, mercaptopurine, theophylline, and cytotoxic chemotherapeutic drugs.

(12) Patients with a history of alcohol or drug dependence or need long-term daily painkillers for any reason.

(13) Patients who have been involved in other clinical investigations within the first 3 months of enrolment.

#### Who will take informed consent? {26a}

Each subject will obtain informed consent or assent from potential trial participants or authorized surrogates.

#### Additional consent provisions for the collection and use of participant data and biological specimens {26b}

Not applicable.

### Interventions

#### Explanation for the choice of comparators {6b}

A total of 98 patients with gout combined with renal calculi who meet the study criteria will be randomized (1:1) to the placebo and sodium bicarbonate group.

